## Design and methods

### Design

WoPaCoM is a study conducted in an Occupational Health Service in the South of The Netherlands that started at the end of 2007. Data gathering was finished in 2012. The customers of this service have their activities in the chemical industry. The two main customer organizations consist of approximately 6,000 workers in several settings, jobs and positions, varying from white and blue collar workers to researchers and administrative personnel. The WoPaCoM study is a two-armed (stratified) randomised controlled trial (with a block size of 4), evaluating the effectiveness of the MPI, including a process evaluation, for decreasing symptoms of fatigue and depression. After the baseline measurement, follow-up measurements at 4, 6 and 12 months are carried out (Figure 1). A total number of 124 participants will be included. The effect of MPI will be compared with care as usual. The ethics committee of the Maastricht University Medical Center found that the study was not subject to the Dutch Medical Research Involving Human Subjects Act (WMO): subjects were not subjected to invasive treatments, the subjects’ privacy was sufficiently guaranteed, and the setting was one in which regular occupational care was evaluated.

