### Randomisation

After having completed the baseline questionnaire, participants were randomly assigned to either the intervention or control group to ensure equal numbers in both groups. Furthermore, the randomisation was stratified to avoid possible confounding. The strata are the customer organization (representing different production plants and organisational structure), income (low, high as defined by the median income in the organization), and gender (male, female). The intervention group received the Minimal Psychological Intervention. The control group received care as usual, being the standard follow-up by the occupational health physician. Mostly this consists of additional consultation and follow-up advice. The principles underlying the intervention (cognitive behavioural therapy and self-management) have been validated in previous research [35,36] and we therefore think that our findings are not substantially biased by the Hawthorne effect. All possible co-interventions were registered in both intervention as well as control group.

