### Effect evaluation

Table 2 provides an overview of the outcome measures. The primary outcome measures in this study are fatigue as measured with the CIS-20 and the level of depression as measured with the Beck Depression Inventory (BDI) [40,41]. Secondary outcome measures in the study are quality of life as measured with the SF-36 [42], Mastery using the Personal Mastery Scale developed by Pearlin and Schooler [43], and General Self Efficacy [44,45]. Sick-leave data were available from official plant registrations. Varying covariates were measured. Information on demographic factors (age, gender, marital status, religion, education, occupation, and income) was collected in the screening phase. Other measures were coping using the active coping, avoidant coping and passive coping scales from the Utrecht Coping List (UCL) [46], anxiety assessed using the anxiety subscale from the Symptom Checklist (SCL-90) [47], co-morbidity using a 24-item chronic conditions list (e.g. heart disease, cancer) and 16-item life-events list where patients report which life events they have experienced in the past year, and how they value these events (positive, negative, or neutral). To check for contamination in the control group, two questions are added in the T3 questionnaire asking whether or not workers in the control group had heard, used parts of, or somehow benefited from the MPI.

**Table 2 T2:** List of instruments (questionnaires/variables)

**Variable/ used instrument**	**Moment in time**				
	**PMCU***	**T0**	**T1**	**T2**	**T3**
Organization	X				
Income	X				
Gender	X				
Age	X				
PHQ-9 [27-29]	X	X			
CIS20 [25,26]	X	X	X	X	X
SF-36 [40]		X	X	X	X
BDI [38]		X	X	X	X
SCL (Anxiety scale) [40]		X	X	X	X
UCL [44]		X	X	X	X
Pearlin & Schooler Mastery [41]		X	X	X	X
Sherer/Bosker (GSE) [42]		X	X	X	X
Prodisq (module C-E) [46,47]		X	X	X	X
Chronic disease		X			X

*PMCU Periodic Medical Check Up.

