### Analysis

Data will be analysed according to the intention to treat principle. Despite participants dropping out of the intervention or not returning follow-up questionnaires, each individual is analysed as randomized (either control or intervention). We tried to encourage (potential) drop-outs to return their questionnaires in order to have complete data as much as possible. But if this was not possible, available (but not complete) data will still be included in the multilevel repeated measures analysis; this type of analysis better allows incomplete data. Finally, in the forthcoming articles, we will give full insight into the response rates at all phases of the study and consideration of the extent to which this might have caused specific biases.

Changes in primary and secondary outcome measures between the intervention and the control group will be analysed using both univariate and multivariate techniques. Models will be adjusted for baseline differences, age, gender, and socioeconomic status. Potential additional confounding factors and effect modifiers (covariates) will be checked separately and when necessary included in the model. If numbers permit, subgroup analyses will study the robustness of the findings across organizations and workers with a low and high income.

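### The primary model is only partly fixed: further covariates enter on an undefined test of need, without limit to pre-randomisation values, and the organisation stratum is left out

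*Protocol article*

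**What the plan says.** The Analysis section of the protocol article gives two sentences on adjustment. The first names a core set: "Models will be adjusted for baseline differences, age, gender, and socioeconomic status". The second opens it: "Potential additional confounding factors and effect modifiers (covariates) will be checked separately and when necessary included in the model". What makes inclusion necessary is not stated, nor are the candidate variables or the time point of their values. The same section announces both univariate and multivariate analyses, and a multilevel repeated measures model for incomplete follow-up.

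Under Effect evaluation, the candidates follow the sentence "Varying covariates were measured". They are demographic factors, three coping scales (UCL), an anxiety subscale (SCL-90), co-morbidity and life events. Table 2 shows the UCL and the anxiety scale at T0 and again at T1, T2 and T3.

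The Randomisation section places allocation after T0: "After having completed the baseline questionnaire, participants were randomly assigned to either the intervention or control group". It stratifies by customer organisation, income and gender. The Design section adds: "Data gathering was finished in 2012".

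**The concern.** In a randomised trial the covariates of the primary model should be known before results by arm can be seen. Here the core is named, but its extension is left to judgement at a time when all outcome data are already collected. Two analysts following the text could report different primary estimates, and each would be within the protocol. If the choice leans towards the more favourable result, the 5% level no longer holds.

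Three details of the wording add to this.

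- The term baseline differences has two readings. It may mean the T0 value of the outcome, which is sound. It may mean imbalances observed between arms, which are chance after randomisation and a poor guide to adjustment.
- Organisation was used to stratify but is not in the core set. Income is covered only if socioeconomic status is taken to mean it.
- Nothing confines covariates to pre-randomisation values. Coping and anxiety are re-measured at T1 to T3, and the intervention teaches self-management and changes in behaviour, so it could move them. Adjusting for those follow-up values would remove part of the effect that the trial is meant to estimate.

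**Working it through.** **Trial size used.** The Power calculation section gives α 0.05, power 0.90, 25 versus 5 percent, and 62 per arm. Read as two proportions, two-sided, with unpooled variance:

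n = (0.25×0.75 + 0.05×0.95) × (1.960 + 1.282)² / 0.20² = 61.7, rounded up to 62.

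With 25% attrition, 62 / 0.75 = 82.7, rounded up to 83. Both figures reproduce. They are not in dispute and only set the size of the simulated trials.

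**Effect of covariate choice on type I error.** The document gives no covariate effects, so these are assumptions: 62 per arm, one endpoint at one time point, no true effect, 4 or 8 independent baseline covariates, and 3,000 trials per scenario. The outcome was 0.5 × (baseline outcome) + ρ × (sum of covariates)/√K + noise with SD 0.8, where K is the number of covariates and ρ is 0.3 or 0.6. The fixed model holds arm and baseline outcome. The last column takes the smallest p-value over all K + 4 models examined: the fixed model, K single-covariate models and the three rule-based models.

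| K, ρ | Fixed model | 10% change in estimate | Imbalance p<0.10 | Outcome association p<0.05 | Most favourable model |
|---|---|---|---|---|---|
| 4, 0.3 | 5.1% | 4.8% | 4.4% | 5.5% | 7.8% |
| 4, 0.6 | 5.7% | 4.5% | 4.5% | 5.9% | 11.3% |
| 8, 0.3 | 5.3% | 5.5% | 4.4% | 6.2% | 9.2% |
| 8, 0.6 | 4.5% | 3.7% | 3.5% | 5.5% | 11.2% |

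A separate simulation used 124 participants, 8 covariates each with coefficient 0.25, and 3,000 trials. It gave 4.3% unadjusted, 4.6% for a fixed full model, 3.0% when adjusting only for covariates imbalanced at p<0.10, and 12.0% for the smallest p-value over ten models (unadjusted, eight single-covariate, full).

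The simulation standard error near 5% is √(0.05×0.95/3000) = 0.4 percentage points. The fixed model is therefore compatible with 5%. Mechanical rules run from 3.0 to 6.2%, and free choice from 7.8 to 12.0%.

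**What follow-up covariates would do, if used.** The document does not plan this, so every input is an assumption. The total effect is the standardised difference that 62 per arm detects with 90% power: (1.960 + 1.282) × √(2/62) = 0.58 SD. A mediator with SD 1 and slope 0.5 on the outcome carries a given share of that effect. The adjusted estimate is then 0.58 × (1 − share), and power comes from 3,000 simulated trials.

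| Share through mediator | Adjusted estimate (simulated) | Power |
|---|---|---|
| none adjusted | 0.58 | about 90% |
| 25% | 0.43 | 78% |
| 50% | 0.29 | 41% |
| 75% | 0.14 | 13% |

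**The case against.** A reader might infer that the protocol plans to adjust for coping and anxiety measured after randomisation. The documents do not support this. Both scales are also taken at T0, before allocation, and adjusting for T0 values is legitimate. Effect evaluation presents Table 2 as a list of outcome measures, so repeated measurement fits their use as outcomes just as well. The sentence "Varying covariates were measured" is followed at once by fixed characteristics such as gender and religion, so its first word more plausibly means various than time-varying. What remains is a use that the wording fails to exclude.

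A reader might also infer that any data-driven selection inflates false positives. The figures above do not show that. Set rules stayed near 5%, and selection on imbalance fell below it. The 8 to 12% belongs to keeping the best result, which the text does not announce. What stands is that the text does not commit to any rule, so it does not rule out that behaviour.

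The core set is named in advance and, on the better reading of baseline differences, largely overlaps a sound model. This article is a condensed document, and a separate analysis plan may define the selection. That would excuse silence. It does not cure a sentence that leaves selection open, because any plan fixing the model would have to override it. Finally, completed data collection does not show that anyone had seen results by arm, and the document does not say.

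**Conclusion.** The concern holds in a limited form. The primary model is partly pre-specified, its extension is undefined, and one of the three stratification factors is missing from it. The estimate can therefore depend on analyst choice. False positives can rise to about 8 to 12% if the most favourable model is kept, against about 5% for a fixed model and about 3 to 6% under mechanical rules. These figures rest on one endpoint, 62 per arm and assumed covariate effects. They come from a single-time-point regression, not the multilevel model. The effect of leaving out organisation was not quantified.

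The loss of effect and power from follow-up covariates illustrates an unexcluded risk. It rests on an assumed effect size and mediated share, and it is not an expected result of the plan. The point merits a change of wording; it does not show that the trial's results will be invalid.

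**What to change.** Replace the two adjustment sentences with one fixed rule:

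- The primary model for each outcome contains arm, the T0 value of that outcome, the three randomisation strata (organisation, income, gender) and age, whatever imbalance is observed. This also settles what baseline differences means.
- Coping, anxiety, co-morbidity and similar variables enter only as T0 or screening values, in one model labelled as a sensitivity analysis.
- Analyses of effect modifiers are labelled exploratory.
- T1 to T3 values are not used as covariates in any effect model. They remain outcomes, including the repeated outcome in the multilevel model, or enter a separate mediation analysis.

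Lock this before arm codes are attached to the outcome data. The cost is wording only: every variable is already collected and no new data are needed. The downside is losing the freedom to add a covariate to the primary model later.

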### Power calculation

Using an individual randomization scheme, assuming an α of 0.05, a 1 – β of 0.90, and a decrease in symptoms of depression and/or fatigue of 25 percent in the intervention group versus a 5 percent decrease in the control group, 62 persons per arm were needed. As we expected that 25% percent would stop participating after baseline (attrition), 83 persons per arm had to be initially recruited [50,51].

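### The 62 per arm matches a comparison of two proportions, but both primary outcomes are continuous scores, so the stated 90% power is not established for either of them

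*Protocol article*

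**What the plan says.** The Power calculation section gives the whole calculation in two sentences. The inputs are "assuming an α of 0.05", "a 1 – β of 0.90" and an effect worded as "a decrease in symptoms of depression and/or fatigue of 25 percent in the intervention group versus a 5 percent decrease in the control group". The result is that "62 persons per arm were needed". Attrition is then added: "25% percent would stop participating after baseline (attrition), 83 persons per arm had to be initially recruited". The section gives no SD, baseline mean, standardised effect, responder definition or named test, and does not say whether the test is one- or two-sided.

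The Effect evaluation section fixes the endpoints: "The primary outcome measures in this study are fatigue as measured with the CIS-20 and the level of depression", the latter measured with the BDI. The Analysis section says how they are compared: "Changes in primary and secondary outcome measures between the intervention and the control group will be analysed using both univariate and multivariate techniques". It names a multilevel repeated measures analysis, with adjustment for baseline differences, age, gender and socioeconomic status. The cut-offs under Setting and recruitment serve eligibility only. The article defines no response or recovery criterion as an outcome.

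**The concern.** A 25% versus 5% fall in symptoms reads as a difference in mean change on a score. A trial cannot be sized on that without knowing how large the difference is relative to the SD, and no SD is given. The stated inputs are enough for a sample size only if 25% and 5% are proportions of participants. A 90% power obtained that way belongs to a comparison of response rates, which the article does not plan.

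What is at stake is how the results are read. The Progress of the study section reports 127 completed follow-ups, against 2 × 62 = 124 needed, so a reader could conclude that a 90% power target was met for fatigue and for depression. The calculation does not support that for either scale. One figure also covers two instruments whose ratio of SD to mean need not be alike.

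**Working it through.** **Inputs.** α = 0.05, power 0.90, 25% versus 5%, 62 per arm and 25% attrition come from Power calculation. Equal allocation comes from Randomisation ("to ensure equal numbers in both groups"). Two-sided testing is my assumption.

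**Step 1: reproduce the stated figure.** Two proportions, unpooled variance:

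n = (z₀.₉₇₅ + z₀.₉₀)² × [p₁(1−p₁) + p₂(1−p₂)] / (p₁−p₂)²

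= (1.960 + 1.2816)² × (0.25×0.75 + 0.05×0.95) / 0.20²

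= 10.507 × 0.235 / 0.04 = 61.73, rounded up to **62**.

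Attrition: 62 / 0.75 = 82.7, rounded up to **83**. Both stated figures are recovered, and the attrition step is correct.

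**Step 2: what 62 per arm detects on a continuous score.**
- Unadjusted, one time point: the two-sample t-test with 62 per arm has 90% power at d = 0.587. The normal approximation, 3.2416 × √(2/62), gives 0.582.
- Adjusted for the T0 score, assumed correlation 0.5: residual variance factor 1 − 0.5² = 0.75, so d = 0.587 × √0.75 = 0.51.
- Effect averaged over three follow-ups and baseline-adjusted, all correlations assumed 0.5: variance factor (1 + 2×0.5)/3 − 0.5² = 0.417, so d = 0.587 × √0.417 = 0.38.

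**Step 3: translate 25% versus 5%.** Read as mean percentage decreases, the difference is 20% of the baseline mean. With CV = SD / baseline mean, which the article does not give, d = 0.20 / CV. Power at 62 per arm, two-sided 0.05:

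| CV (assumed) | d | Unadjusted, one time point | Baseline-adjusted (r = 0.5) | Mean of three follow-ups (all r = 0.5) |
|---|---|---|---|---|
| 0.3 | 0.67 | 96% | 99% | >99% |
| 0.4 | 0.50 | 79% | 89% | 99% |
| 0.5 | 0.40 | 60% | 72% | 93% |
| 0.7 | 0.29 | 35% | 45% | 69% |

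The largest CV that still gives 90% power is 0.20/0.587 = 0.34 unadjusted, 0.20/0.51 = 0.39 baseline-adjusted, and 0.20/0.38 = 0.53 for the three-visit average.

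**Step 4: the other reading.** If 25% and 5% were meant as proportions crossing a cut-off on a normally distributed score with equal SDs (an assumption), they imply d = 1.645 − 0.674 = 0.97. Power on the score at 62 per arm would then exceed 99.9%.

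Across these readings power runs from 35% to above 99.9%, so the stated inputs do not determine it for either primary outcome.

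**The case against.** The strongest reply has four parts.

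- **The formula is not named.** The section cites two sources that are not at hand. A comparison of means with an undisclosed SD of about 0.34 of the baseline mean would also give 62, and other common two-proportion variants give somewhat different numbers. This stands, so the origin has to be put as an inference. It is a strong one: the stated inputs alone return 62 under a standard formula, whereas the means route needs an unstated SD ratio that happens to land on the same number and serves two scales at once.
- **Sizing on a dichotomised outcome and then analysing the score is usually conservative.** This also stands, as Step 4 shows. It means the error could lie on the safe side; it does not make 90% the right figure.
- **Unadjusted t-test figures understate the planned analysis.** Correct. The planned model adjusts for baseline differences and uses repeated measurements. A reader might infer that 90% power requires a CV of at most 0.34. That limit applies only to an unadjusted single-visit comparison and moves to 0.39 or 0.53 under the assumptions above.
- **Recruitment and data collection are closed, so no design decision can change.** True, and this limits the remedy to restating the claim. The figure is still the article's only statement of what the trial could detect.

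**Conclusion.** The point holds as a mismatch between the power statement and the endpoints. The 62 per arm is reproduced exactly by a two-sided, unpooled two-proportion formula, while the plan compares changes in two continuous scores and defines no responder endpoint. The stated 90% power is therefore not established for the CIS-20 or the BDI.

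The size cannot be fixed from the article. If the assumption means a difference of 20% of the baseline mean, power at CV 0.5 is 60%, 72% or about 93% depending on the analysis, and at CV 0.7 it is 35%, 45% or 69%. These rest on assumed CVs and correlations of 0.5.

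Two stronger readings are tempting and unsupported. One is that the trial is underpowered: with a small CV, or under the responder reading, power exceeds 90%. The other is that fatigue is over-powered and depression under-powered: the article gives no mean or SD for either scale, so nothing in it separates the two.

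**What to change.** Replace the power statement with the detectable difference, for example: *62 analysed per arm gives 90% power (two-sided 0.05) for a standardised difference of 0.59 in an unadjusted single-time-point comparison, or about 0.51 adjusted for the T0 score (assumed correlation 0.5); the repeated measures analysis may detect a smaller difference.*

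Then take the T0 means and SDs of the CIS-20 and the BDI, pooled over arms, and state for each scale separately what a 20-point difference in percentage decrease is in scale points and what power 62 per arm gives for it. If the 25% and 5% were in fact response proportions, say so, define the response, and state that it is not the primary outcome.

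The cost is a text change and a short calculation from T0 data already collected, without reference to allocation. No extra patients are needed, and the attrition step and planned analysis stay as they are. The downside is that the stated power may become less favourable for one of the scales.

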### Process evaluation

The aim of the process evaluation is to assess how the intervention is perceived e.g. appreciated by all participants (i.e. workers and nurses). Using the framework of Jonkers and colleagues [19], it focuses on the following outcomes. The reach of the intervention, being defined as the proportion of the intended target population that actually participated in the intervention. The dose delivered, defined as the completeness of the intervention and number and duration of the intervention visits. Dose received, is described in two concepts, namely exposure and satisfaction. Exposure is the extent to which participants actively engage with and are receptive to the intervention, and satisfaction is defined as participants's satisfaction with the intervention [52]. Barriers are described as the extent to which problems were encountered during the intervention. Data were collected using questionnaires filled out by nurses after every intervention visit, by means of checklists that were kept by the nurse for every participant (regarding which steps of the intervention had been taken), and by questionnaires filled out by participants after the end of the intervention.

## Discussion

### Progress of the study

In 2007, based on the occupational health service’s experience, it was estimated that it would take approximately two years to recruit participants. However, both the participation rates to the medical check-ups and the return rates of the screening questionnaires were smaller than expected and decreased substantially, particularly during the first phase of the economic crisis in Europe (2009). Increased perceptions of job insecurity might underlie these trends. Increasing efforts were needed to keep participants involved in the intervention itself, but also during the one-year follow-up. We ended inclusion in the study in April 2011 and the intervention has been administered to all participants in the intervention arm. Data collection was completed in June 2012. 127 Participants have completed their follow-up questionnaires. Of all participants initially included in the study 93% were male and 7% female (which was expected given the gender distribution in the plants). As per the stratified and blocked design, there is an equal number of intervention and control participants in the different strata.

